#### Handling of dropouts

2.2.3

(1) Criteria for dropout

Patients who have provided informed consent, been screened and randomized for the trial, but for any reason do not complete the treatment and observation period as outlined in the study protocol will be considered dropouts.

(2) Handling of dropout cases

1) After a patient drops out, the researcher should contact the patient via home visits, scheduled follow-ups, phone calls, or letters to inquire about the reason for dropout, record recent sleep patterns, and complete any assessments that can be performed.

2) For patients who drop out due to allergies, adverse reactions, or treatment ineffectiveness, appropriate treatment measures should be taken according to their condition.

3) All dropout cases should be properly documented, both for archival purposes and for the required analysis in statistical evaluation. No additional patients will be recruited to replace dropouts.

#### Trial termination

2.2.4

(1) If a serious adverse event occurs, or the researcher determines the trial should be stopped for this reason.(2) If the patient’s condition worsens, or if other issues arise during the trial that affect observation, the researcher may decide to stop the trial.(3) If significant protocol deviations occur during the implementation of the clinical trial, such as poor adherence to the protocol, making efficacy evaluation difficult, the trial may be stopped.(4) If the participant expresses unwillingness to continue with the trial and requests to withdraw.

### Sample size

2.3

Based on the type of study, the sample size is calculated using PASS 15.0 software. The PSQI score of insomnia patients is chosen as the outcome measure. Based on literature and preliminary experimental results, the average PSQI score for the drug control group is 10.76 ± 3.32, and it is expected that the PSQI score in the insomnia group will decrease by 2.63 points. An effect size of 0.8 is used, with α = 0.05 and power = 0.9. The calculated sample size for each group (AA group, SAA group, control group) is N1 = N2 = N3 = 52. Considering a 20% dropout rate, the total sample size required is N1 = N2 = N3 = 65. According to previous reports [5], the prevalence of insomnia in adolescents is 20%, so the sample population is (N1 + N2 + N3) ÷ 20% = 975, then the sample population should be more than 975.

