#### Inclusion criteria

2.2.1

(1) The diagnosis met ICSD-3 criteria, characterized by difficulty initiating sleep (>20 minutes), difficulty maintaining sleep, or early morning awakening despite adequate sleep opportunity, accompanied by daytime functional impairment. These symptoms occurred at least three times per week and persisted for more than three months.(2) Age between 13–18 years;(3) PSQI score > 7;(4) No psychiatric medication treatment;(5) No communication or cognitive impairments;(6) Signed informed consent.

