#### Intergroup comparison methods

2.9.1

For normally distributed measurement data meeting the assumptions of parametric tests, within-group pre- and post-treatment comparisons will be conducted using paired-sample t-tests. Intergroup comparisons will employ one-way ANOVA. Non-normally distributed measurement data will be analyzed using nonparametric rank-sum tests, and categorical data will be assessed via chi-square tests or Fisher’s exact probability test. These comparisons will evaluate the therapeutic effects of auricular acupressure.

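### The 52 per group does not follow from the stated effect size, alpha and power (it is larger than they require), and the inputs are not tied to any contrast in this trial

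*Protocol article*

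**What the plan says.** Section 2.3 of the protocol article sizes the trial on the PSQI with PASS 15.0, citing literature and preliminary results. Its inputs are:

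- a reference value: "the average PSQI score for the drug control group is 10.76 ± 3.32";
- an expected change: "it is expected that the PSQI score in the insomnia group will decrease by 2.63 points";
- the design parameters: "An effect size of 0.8 is used, with α = 0.05 and power = 0.9".

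The result is 52 in each of the AA, SAA and control groups, then 65 each after 20% dropout. With an insomnia prevalence of 20%, "then the sample population should be more than 975".

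Section 2.3 does not name the test, the sidedness, the type of effect size or any multiplicity adjustment. For the between-group test, section 2.9.1 says: "Intergroup comparisons will employ one-way ANOVA". Section 2.7 describes the arms as sleep hygiene education alone, education plus AA, and education plus SAA. Section 2.2.1 requires "No psychiatric medication treatment".

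**The concern.** There are two problems in the same paragraph.

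First, the printed inputs and the printed output do not match. A reader who enters 0.8, 0.05 and 0.9 into any ordinary two-group or three-group calculation gets a number well below 52.

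Second, the inputs do not describe a comparison that this trial makes. The reference group is a drug group, but no arm receives a drug. The insomnia group does not identify an arm, because all three arms consist of adolescents with insomnia. The 2.63 points are worded as a decrease, yet the effect size of 0.8 is evidently 2.63 divided by 3.32, so they serve as a standardised difference without being assigned to AA v SAA or AA v education.

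What is at stake is how the result is read. The 90% power is not attached to any named contrast or difference. SAA shares the points, the pressing instruction and the education with AA. If that comparison is null, a reader could take it as a negative result from a trial with 90% power, without knowing for what difference.

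**Working it through.** **Inputs** (section 2.3 unless noted): effect size 0.8; alpha 0.05; power 0.90; SD 3.32; change 2.63; three arms, 1:1:1 (section 2.5); one-way ANOVA (section 2.9.1). Two-sided testing is assumed.

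**Type of effect size.** 2.63/3.32 = 0.792, so 0.8 is evidently a standardised mean difference d.

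**Steps after 52.** 52/(1 − 0.20) = 65. 3 × 65 = 195, and 195/0.20 = 975. Both reproduce, so the discrepancy lies in the 52 itself.

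**Two-sample t-test.** Power is taken from the noncentral t distribution with 2n − 2 degrees of freedom and noncentrality d√(n/2). At d = 0.8, n = 33 gives 0.893 and n = 34 gives 0.902, so 34 per group.

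**Bonferroni for three pairs.** The same formula at alpha 0.05/3: n = 43 gives 0.895 and n = 44 gives 0.902, so 44 per group.

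**Three-group one-way ANOVA.** Power is taken from the noncentral F distribution with 2 and 3n − 3 degrees of freedom and noncentrality 3n·f².
- One arm differs by 0.8 SD and the other two are equal: f = 0.8√2/3 = 0.377. n = 30 gives 0.893 and n = 31 gives 0.903, so 31.
- Middle arm halfway: f = 0.8/√6 = 0.327. n = 40 gives 0.896 and n = 41 gives 0.903, so 41.
- 0.8 read as f itself: 8 per group.

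Using 0.792 in place of 0.8 raises these figures by at most 1.

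**Routes that do reach 52**

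| Route | Result | What the protocol does not state |
|---|---|---|
| ANOVA, middle arm halfway, alpha 0.05/3 | power 0.899 at 51, 0.905 at 52 | an alpha split |
| Tukey, all three pairs significant, arms equally spaced 0.792 SD apart | power about 0.895 at 51, 0.903 at 52 | the Tukey test, and an outer-arm gap of 2 × 2.63 = 5.26 points |
| 41 per group, dropout applied here and again later | 41/0.8 = 51.25, so 52 | a second dropout allowance |

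**What 52 evaluable per arm delivers (pairwise t-test)**

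| Difference | Unadjusted 0.05 | Bonferroni, three pairs |
|---|---|---|
| 0.8 SD | 98% | 95% |
| 0.73 SD (0.7312 × 3.32 = 2.43 points) | – | 90% |
| 0.64 SD (0.6418 × 3.32 = 2.13 points) | 90% | – |
| 0.5 SD (1.66 points) | 71% | 55% |
| 0.4 SD (1.33 points) | 52% | 35% |

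The 0.5 and 0.4 SD rows are illustrative. The protocol gives no expected AA–SAA difference.

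**Screening.** 975 × 0.20 = 195 only if every student with insomnia is eligible and consents. If a share s of them does, 975 yields 195s participants, and 195 participants need 975/s students. The protocol gives no s. As an assumed range, s = 0.9 gives about 176 randomised (1,084 to screen), s = 0.7 about 137 (1,393), and s = 0.5 about 98 (1,950).

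**The case against.** The strongest reply has four parts.

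1. **52 may be the result of a legitimate calculation.** Section 2.3 names no test, and importing ANOVA from section 2.9.1 is an inference. An article may leave the PASS procedure and any alpha split to the full protocol. This stands in part: 52 is not impossible, and more than one undocumented route reaches it. But the paragraph prints alpha as 0.05 with no adjustment, and those inputs do not give 52 under any standard test tried. The point concerns what is printed, not detail left out.

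2. **The direction is harmless.** This stands. A reader might infer from a sample size that cannot be reproduced that the trial is underpowered. The documents do not support that: every ordinary reading of the stated inputs needs fewer than 52. Lower power arises only at differences smaller than 0.64 SD, and the protocol neither assumes nor excludes such differences for AA v SAA.

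3. **The drug group may be an external reference.** The values are attributed to literature and preliminary work, and the decrease may mean lower than that reference. This is possible, so it would go too far to say that 2.63 is certainly a within-group fall. On either reading, however, it is not stated as a difference between two arms of this trial.

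4. **975 is given as a floor.** This stands. A reader might infer that screening will fall short, but the eligible-and-consenting share is unknown, so that cannot be shown.

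**Conclusion.** The point holds as a should-fix matter of justification. The 52 per group does not follow from effect size 0.8, alpha 0.05 and power 0.9: the same inputs give 34 (t-test), 31 to 41 (ANOVA) or 44 (Bonferroni for three pairs). The error is conservative, with power at 0.8 SD of about 98%, or 95% after Bonferroni, in place of the stated 90%. The reference group and the 2.63-point change are not linked to AA v SAA or AA v education, so the stated power belongs to no contrast that the trial tests.

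This rests on reading 0.8 as a standardised mean difference, which 2.63/3.32 supports, on two-sided testing, and on 52 evaluable participants per arm. The screening figure is secondary: 975 is correct arithmetic for a minimum with no allowance for ineligibility or refusal.

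**What to change.** Keep 65 per arm and rewrite section 2.3:

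- Name the contrast, the test, the sidedness, the type of effect size and any multiplicity adjustment actually used to obtain 52. Which contrast the trial is sized on is the sponsor's choice.
- Replace the drug-group and insomnia-group wording with the source of the SD and an expected between-arm PSQI difference for a contrast the trial tests.
- State what 52 evaluable per arm delivers: 90% power for a pairwise difference of 0.64 SD (2.13 points) at unadjusted two-sided 0.05, or 0.73 SD (2.43 points) with Bonferroni for three pairs. A null sham comparison then cannot be read as 90%-powered for smaller differences.
- Label 975 as a minimum, or divide it by an assumed eligible-and-consenting share shown as a range.

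The cost is a text change and restated figures. No randomised participants are added; more screening questionnaires may be needed if the share is well below 1.

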### Ethics and trial registration

2.4

The ethical review and informed consent materials for this study are approved by the Ethics Committee of the Nanjing University of Chinese Medicine Affiliated Hospital (Jiangsu Provincial Hospital of Chinese Medicine) on February 5, 2024. The approval number is 2024NL-010-02. This study has also been registered with the International Traditional Medicine Clinical Trial Registry, approval number ITMCTR2024000343. All invited participants and their legal guardians will receive a written informed consent document explaining the goals of the study and the participants’ rights. Participation is entirely voluntary.

### Randomization

2.5

After screening based on the inclusion and exclusion criteria, eligible adolescent insomnia patients will be randomly assigned in a 1:1:1 ratio to the AA group, SAA group, or control group. The randomization sequence will be generated by researchers who are not involved in the trial implementation or statistical analysis using SPSS 25.0 software. The sequence will be hidden using the envelope method, and each envelope will contain the randomization order for patient allocation. A designated person will be responsible for patient inclusion, and patients will receive the corresponding envelope in the order of enrollment.

### Blinding

2.6

To further improve the effectiveness of the blind method, participants in both the AA group and the SAA group were uniformly informed that they needed to apply pressure after applying the skin-colored tape, thereby reducing patients’ sensitivity to group differences. Additionally, the skin-colored tape used in both the AA and SAA groups was identical in appearance and texture, and was fixed by researchers at the same ear acupoint locations, ensuring that they could not be distinguished visually. Participants, evaluators, and statisticians will remain blinded throughout the study to minimize potential bias arising from procedural differences. As acupuncturists are responsible for delivering the AA and SAA interventions, they cannot be blinded to group allocation; however, they will not participate in outcome assessments. Evaluators will remain fully blinded to group assignments. They will solely be responsible for data collection and are prohibited from discussing treatment-related information with participants.

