**Methods:**

This study is a single-center, double-blind, randomized controlled trial conducted in Nanjing, China. Participants are students from junior and senior high schools in Nanjing. A multi-stage stratified cluster sampling method is used to recruit students from 7th and 8th grades (junior high) and 10th and 11th grades (senior high). Baseline data will be collected using the Chinese version of the Pittsburgh Sleep Quality Index (PSQI), Beck Depression Inventory (BDI), Adolescent Sleep Hygiene Scale (ASHS), Children’s Depression Inventory (CDI), Adolescent Self-rating Life Events Checklist (ASLEC) and Adolescent Sleep-Wake Scale (ASWS), and insomnia patients will be identified. Adolescents who met the inclusion and exclusion criteria and whose guardians signed informed consent forms will be enrolled in the study. They will be randomly assigned to one of three groups: AA group, sham auricular acupressure (SAA) group, and control group. The treatment lasted for 8 weeks, with follow-up assessments at 3 and 6 months post-treatment. The primary outcome measures are PSQI and BDI scores, while secondary outcome measures included ASHS, CDI, ASLEC, and ASWS scores.

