#### Control group

2.7.1

Sleep hygiene education: Actively communicate with the patient to understand the causes of insomnia, provide targeted guidance and explanations to alleviate negative emotions, and provide a sleep education manual. This includes informing patients about the importance of sleep, guiding them to create a good sleep environment, changing poor sleep habits, and engaging in regular physical exercise. The recommended exercise regimen consists of running (moderate-intensity aerobic activity) with a frequency of three sessions per week (24). Follow-up will be conducted regularly using ASHS, PSQI, ASWS, CDI, and BDI scales to assess sleep and psychological health. If the patient shows signs of depression, appropriate treatment will be provided.

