#### AA group

2.7.2

In the AA group, AA will be applied in addition to sleep hygiene education. Points: Shenmen (TF4, located in the triangular fossa, above the division of the ear lobe), Subcortex (AT4, on the inner side of the ear), Endocrine (CO18, anterior lower part of the ear canal), Liver (CO12, behind the lower part of the ear), Heart (CO15, central part of the ear), Kidney (CO10, below the upper and lower branches of the ear lobe) (**Figure 3**). These points will be carefully located according to the guidelines in the “Illustrated Ear Acupuncture” by Shanghai Science and Technology Publishing House. After evaluation, the most sensitive areas will be treated with ear acupressure beans. Each session will treat one ear, with changes to the other ear every 3 days. Patients will be instructed to press the acupressure beans 3–5 times per day, 1–2 minutes per session. The treatment will last for 8 weeks, followed by follow-ups at 3 months and 6 months.

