#### SAA group

2.7.3

In the SAA group, SAA will be applied in addition to sleep hygiene education. The same points as in the AA group will be selected, but adhesive tapes without seeds will be placed on the ear. To reduce intergroup differences and improve the effectiveness of the blinded method, the SAA group will also be required to press the ear patches according to uniform instructions to maintain consistency with the AA group’s operating procedures. This will prevent patients from easily guessing the groupings and ensure similarity in the operating experience between the two groups during the intervention. At the end of the study, patients will receive the same AA treatment as the ear acupressure group.

In addition, to minimize dropout rates and enhance participant adherence, researchers will engage with participants during each replacement of the ear acupressure beans. Participants will be reminded to apply pressure according to the prescribed frequency and duration, and to regularly monitor the placement and condition of the ear acupressure beans. These measures aim to encourage continued compliance with the study protocol.

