## Discussion

3

This study is a single-center, double-blind, randomized controlled trial aimed at evaluating the efficacy of AA in improving sleep and observing its impact on the occurrence of depression following insomnia in adolescents. The goal is to provide new insights into the prevention of adolescent depression.

Insomnia is closely related to depression (34). Adolescence is a critical period for the development of personality and traits, during which adolescents also experience a “perfect storm” of sleep changes. Many factors contribute to the increased susceptibility to insomnia during this period. The reduced sleep drive in adolescence, the extended intrinsic circadian cycle of the endogenous clock, and the delayed secretion of melatonin interact with external factors such as participation in extracurricular activities, heavy homework, use of electronic devices at night, and early school start times, leading to delayed sleep onset and reduced sleep duration. Over time, these factors result in the occurrence of insomnia (35, 36). In China, the education system differs from that of other countries, with heavy homework loads and dense curricula, making academic pressure an inevitable source of stress for Chinese adolescents (37), which is one of the key factors contributing to insomnia (38).

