However, two critical research gaps persist: only two registered auricular acupressure trials target adolescents (ITMCTR2024000343, ITMCTR2100005080), while prospective preventive studies remain absent. This school-based intervention demonstrates feasibility through standardized protocols requiring minimal training, brief 5–7 minute sessions during breaks, and low-cost materials. The combined professional administration and parent-supervised home application ensures adherence without disrupting academics, offering a replicable model for educational settings.

This study used the Chinese version of the PSQI to evaluate adolescents’ sleep quality. the psycholemtric properties of the Chinese version of the PSQI have been validated in a large sample of 5,399 by Cheng (27). The scoring algorithm for the sleep duration item retained the original recommended hours for adults rather than reflecting the longer sleep needs of adolescents. Nevertheless, the findings from the confirmatory factor analysis supported a three-factor model, with configural and metric invariance across gender and age groups, indicating that the Chinese version of the PSQI is a valid and reliable measure of sleep quality in non-clinical adolescent populations.

This study also has some limitations. First, the study’s generalizability may be limited by its exclusive focus on secondary school students in Nanjing due to budgetary and staffing constraints, which could introduce selection bias. This may introduce selection bias. Second, this is a single-center design, and single-center trials often involve a homogeneous sample, limiting generalizability and potentially introducing experimental bias. Future studies should consider more influencing factors and further validate and explore the results in larger sample populations. Third, the study outcomes rely on self-report questionnaires, which, although widely used, may still be subject to subjective biases.

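### Participant blinding is claimed for the whole trial but is described only for AA and SAA; the education-only arm is open, so AA v control is an unblinded comparison on self-reported outcomes

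*Protocol article*

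**What the plan says.** The label covers the whole trial. The Abstract (Methods) says "This study is a single-center, double-blind, randomized controlled trial conducted in Nanjing, China", and the Discussion opens with "This study is a single-center, double-blind, randomized controlled trial aimed at evaluating the efficacy of AA". Section 2.6 (Blinding) adds: "Participants, evaluators, and statisticians will remain blinded throughout the study to minimize potential bias arising from procedural differences". None of these sentences is limited to particular arms.

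The measures behind the claim are narrower. Section 2.6 describes one pressing instruction for both ear-treatment arms, the same ear points, and matching tape: "the skin-colored tape used in both the AA and SAA groups was identical in appearance and texture". It also discloses that the acupuncturists know the allocation and take no part in outcome assessment.

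The arms are:
- Control (2.7.1): "Sleep hygiene education: Actively communicate with the patient to understand the causes of insomnia", with a manual and exercise advice. No tape or sham is described.
- AA (2.7.2): "In the AA group, AA will be applied in addition to sleep hygiene education".
- SAA (2.7.3): the same education and the same points, but "adhesive tapes without seeds will be placed on the ear".

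PSQI and BDI are the primary outcomes (2.8.1). The limitations paragraph of the Discussion acknowledges that "the study outcomes rely on self-report questionnaires". Section 2.9.1 compares groups by one-way ANOVA, presents these comparisons as the evaluation of AA's therapeutic effect, and does not name AA v SAA, or any other pair, as the contrast that carries that conclusion.

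**The concern.** A blinding statement tells the reader which comparisons are protected from expectation. Here it is made for all participants, while one arm of three has no described means of being blinded. Two of the three pairwise contrasts, AA v control and SAA v control, are therefore open at participant level.

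This matters because the participant is also the rater. An evaluator who does not know the allocation protects a rating that the evaluator makes. That does not help when a student who knows that he or she has, or lacks, an ear treatment scores his or her own sleep and mood.

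AA v control also mixes several things: the specific effect of bead pressure, expectation, and extra contact at each replacement. Since 2.9.1 does not say which contrast answers the efficacy question, a significant three-arm result that comes from the control arm could be read, under the double-blind label, as blinded evidence for AA.

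**Working it through.** **Step 1. Set the claim against the measures.** The article gives no figure to reproduce here, so the main check is a comparison of text.

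| Arm | On the ear | Pressing instruction | Masking described |
|---|---|---|---|
| AA (2.7.2) | tape with bead | yes | yes, against SAA (2.6) |
| SAA (2.7.3) | tape, no seed | yes, same as AA | yes, against AA (2.6) |
| Control (2.7.1) | nothing described | none | none |

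It follows that:
- AA v SAA has masking measures at participant level.
- AA v control and SAA v control have none.

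That controls can recognise their arm is inferred from treatment they can see. No sentence says so, and the consent wording is not shown. However, the article describes nothing that would conceal it.

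**Step 2. Ask whether evaluator blinding covers the gap.** Section 2.6 confines evaluators to data collection. Section 2.11 has paper questionnaires handed to participants, and the Discussion describes the outcomes as self-reported. So it does not.

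**Step 3. Contact.** The treated ear changes every 3 days for 8 weeks (2.7.2): 56 / 3 = 18.7, or about 18 changes. Section 2.7.3 has researchers engage with participants at each replacement, and 2.7.1 gives controls no matching schedule. The count is approximate, because the Discussion also mentions home application supervised by parents.

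**Step 4. Illustrate the consequence.** The size of the expectation effect is an assumption; the documents give none. Inputs:
- n = 52 per arm after dropout, and SD 3.32 for PSQI (both from 2.3);
- alpha 0.05, taken as two-sided (2.3 does not state sidedness);
- no specific AA effect;
- a shift of d SD shared by AA and SAA, with d = 0.3 to 0.5.

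Two-sample t-test, AA v control: non-centrality = d × √(n/2) = d × √26 = 5.099d, with df = 102 and critical t = 1.983.

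Three-arm ANOVA with means (0, d, d): non-centrality λ = n × (2/3) × d², with df = 2 and 153 and critical F = 3.055.

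| d | PSQI points (d × 3.32) | t non-centrality | P(significant), t-test | λ | P(significant), ANOVA |
|---|---|---|---|---|---|
| 0.3 | 1.0 | 1.53 | 0.33 | 3.12 | 0.33 |
| 0.4 | 1.3 | 2.04 | 0.52 | 5.55 | 0.54 |
| 0.5 | 1.7 | 2.55 | 0.71 | 8.67 | 0.75 |

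With no shift each probability would be 0.05.

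A check on the points scale (normal approximation, standard error = 3.32 × √(2/n)) covers smaller shifts and the full 65 per arm:

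| Assumed shift, PSQI points | 52 per arm | 65 per arm |
|---|---|---|
| 0.5 | 0.12 | 0.14 |
| 1.0 | 0.34 | 0.40 |
| 1.5 | 0.64 | 0.73 |

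Under the same assumptions AA and SAA share the shift, so their expected difference is zero and AA v SAA stays at 0.05.

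**The case against.** The strongest reply is that the sentence in 2.6 was meant for AA and SAA only. The sentences before it concern that pair, and its closing reference to procedural differences fits them. On that reading the fault is a missing qualifier. This is fair as to intent. But the text does not carry the restriction, and the Abstract and Discussion apply the label to the whole trial.

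A second reply is that the design already contains the right tool. SAA receives the same education, points, tape and instruction, and exists to separate expectation and contact from specific effect. An add-on education arm cannot be masked and is a legitimate third arm. This stands. The choice of arms is not at fault, and the fix relies on the sham arm.

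Third, self-report bias is already listed as a limitation. That is true, but the open control arm is not.

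A reader might infer more than the article supports:
- *That AA v SAA is unblinded too*, because a bead can be felt or classmates compare. Both are plausible, but neither is stated. The documents describe masking for that pair and do not show that it fails.
- *That the unblinded acupuncturists defeat the label.* Their status is disclosed, and they do not assess outcomes.
- *That the ANOVA claims equal protection for every contrast.* Section 2.9.1 makes no statement about bias.
- *That a check of participants' allocation guesses has been omitted.* A condensed article may leave this to the full protocol or analysis plan.

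**Conclusion.** The concern holds as an inaccurate blinding statement with a consequence for inference. Participant blinding is described for AA v SAA only. AA v control and SAA v control are open, and because PSQI and BDI are self-reported, blinded evaluators do not protect them. AA v SAA is left intact as the contrast for the specific effect.

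The 33% to 71% range shows how far a modest shared expectation effect could carry AA v control. It rests on an assumed 0.3 to 0.5 SD and is not evidence that this trial is biased; a smaller shift of 0.5 points would give 12% at 52 per arm. The textual conclusion depends on none of these figures. It rests only on the arm descriptions and on the inference that participants can see whether they have tape on the ear.

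The correction should be made: it costs little and changes what AA v control can be said to show.

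**What to change.** 1. In the Abstract (Methods), section 2.6 and the opening of the Discussion, limit participant blinding to AA v SAA and describe the education arm as open. Blinding of evaluators and statisticians can stay as stated.
2. In 2.9.1, name AA v SAA as the contrast for the specific effect of AA. Label AA v control as an unblinded comparison that combines specific effect, expectation and contact.
3. In the limitations paragraph, add that the control arm is open and that the outcomes compared with it are self-reported.

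The arms, the sample size and the data collected do not change. The cost is a few sentences and a less favourable design label.
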